### 6.5 Missing Data

The analysis will require to impute missing values, intermittent missing side effects scores, and dropouts.

The distribution and pattern of missing values will be assessed using tables and plots (using the R package `VIM`; Templ et al. (2017)), giving first hints whether the missing completely at random (MCAR) assumption holds.

**Type of missingness** Missing at random (MAR) is assumed, and data will be imputed applying multivariate imputation by chained equations (MICE) using the R package `mice` (van Buuren and Groothuis-Oudshoorn (2011); van Buuren (2012)).

**Imputation model** Imputations for continuous data will be generated with the predictive mean matching method (pmm). For binary data a logistic regression model, for factors with more than two levels a multinomial logit model, and for ordered factors (>2 levels), an ordered logit model will be used.

**Predictor variables** For the analysis of **Research Question 1a** and the concomitant sensitivity analyses, the following variables will be used as predictors in the imputation process of missing values:

- EAT score obtained immediately after the effectiveness briefing (EAT\_1b)
- effectiveness briefing group (EXPBRIEF)
- side effects briefing group (SIDEBRIEF)
- EAT at baseline (EAT\_BL)
- gender (pers\_1\_2)
- age (age)
- duration of pain at first visit (painduration)
- pain bothersomeness at baseline (nrs\_1a\_2)
- depression (PROMIS\_BL\_depression.theta)
- CARE score (CARE\_1a\_red1)

For the analysis of **Research Question 1b** and the concomitant sensitivity analyses, the following variables will be used as predictors in the imputation process of missing values:

- pain intensity measured at the end of the acupuncture treatment (nrs\_8\_1)
- effectiveness briefing group (EXPBRIEF)
- side effects briefing group (SIDEBRIEF)
- pain intensity at first visit (screeningb\_1a\_4a)
- baseline optimism (LOT\_BL\_optim)
- baseline pessimism (LOT\_BL\_pessim)
- acupuncture therapist (acupuncturist)
- gender (pers\_1\_2)
- age (age)
- duration of pain at first visit (painduration)
- pain bothersomeness at baseline (nrs\_1a\_2)
- depression (PROMIS\_BL\_depression.theta)
- CARE score (CARE\_1a\_red1)

**Variables that are functions of other (incomplete) variables** There is no transformation, combination, or recoding of any variable involved. Hence, no passive imputation or post-processing of imputed values is required.

**Order in which variables will be imputed** Since there are no interactions or transformations, the visiting scheme is not important (except for efficiency) as long as each variable in the data set is visited often enough. Setting the number of iterations to 50 should preclude any issues with respect to visiting (see van Buuren and Groothuis-Oudshoorn (2011), Section 3.6).

**Starting imputations and number of iterations** The number of iterations will be set to 50. To facilitate reproducibility, a seed for the random number generator will be set for all steps involving a random mechanism.

**Number of imputed data sets** The number of imputation will be set to  $m = 50$  in order to minimize simulation error.

**Analysis model** The analysis models are described in Section 6.2.

**Reported values** Pooled results, *i.e.* the average of the estimated coefficients (slope or effect), for multiple imputation adjusted confidence intervals (Rubin, 2004, pp. 76–77),  $p$ -values, the fraction of missing information, and the proportion of total variance attributable to missing data will be reported.

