### 4.3 Analysis Population

- For research question 1a, there are very few patients who did not fill in the baseline questionnaire. An intention-to-treat analysis will be performed using multiple imputation (cf. Section 6.5) to handle missing values.
- For research questions 1b, an intention-to-treat analysis will be performed using multiple imputation (cf. Section 6.5) to handle missing values.
- For research questions 2, an intention-to-treat analysis will be performed (no missing data handling needed, cf. Section 6.2.3).
- In a sensitivity analysis (cf. Section 6.4.1), per-protocol analyses will be done using a complete-case data set (research questions 1a and 1b). In addition, to assess the influence of protocol deviations (cf. 6.4.2), the analyses will be repeated without patients that used opioids (for research question 1b), and only with patients that had at least 6 out of the 8 acupuncture treatment sessions (for research question 1b), respectively.

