## 6 Analysis

### 6.1 Outcome Definitions

The three primary outcomes are

- 1a) Expectation of acupuncture treatment (questionnaire "P2 EAT", now called ETS, but will be labelled with EAT in this SAP), a score based on 5 questions having each 4 levels. It can range from 5 to 20. The questionnaire is filled in by the patients at baseline before the treatment (*i. e.* the briefing by the study doctor), immediately after the treatment, and once more after the 4th acupuncture session (in week 2).
- 1b) Average pain intensity over the last 7 days after 4 weeks at the end of the treatment (questionnaire "P7.2 NRS"). As a measure, a numeric rating scale (NRS) is used in a self-reporting fashion. The NRS has 11 discrete levels from 0 (no pain) to 10 (worst pain possible). The NRS is filled in at baseline (before the treatment), after two weeks, and at the end of the acupuncture sessions. Note that due to eligibility criteria, only patients with an NRS value  $\geq 4$  were included in the study. Accordingly, the baseline values of pain intensity lie within the range of 4–10.
- 2) The side effects score after each acupuncture session (questionnaire "P9 Nebenwirkungen"). A self-report questionnaire with 13 questions and 4 levels each (0 to 3) is used, thus the values range from 0 to 39 per session. As a secondary outcome, the total side effect score for each patient, adjusted for the number of acupuncture sessions that the patient actually received, will be used.

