### 6.6.2 Research question 1b

A second ANCOVA using the pain intensity obtained after the 4th acupuncture session (in week 2) as outcome will be performed. The covariates and adjusting variables will be as described in Section 6.2.2.

### 6.6.3 Research question 2

A secondary outcome for research question 2 is the total side effect score for each patient, which will be adjusted for the number of acupuncture sessions that the patient actually received minus 1. For a patient with the number of sessions given by  $N_s$ , the outcome is thus

$$\text{Total score} = \frac{(\text{Score}_1 + \text{Score}_2 \dots + \text{Score}_{N_s-1})}{N_s - 1} \cdot 7.$$

As this may lead to total score values that are non-integers, the total score will be rounded to the next integer. A zero-inflated negative binomial model with SIDEBRIEF and gender (`pers_1_2`) will be

used. As for the primary analysis (Section 6.2.3), the result from the zero-inflated negative binomial regression will be reported as the ratio of side effect scores with 95% confidence interval and  $p$ -value. In addition, adjusted means of the total side-effects scores with 95% confidence intervals will be reported for each treatment group, where the gender effect will be weighted with 0.5.

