#### 6.6.5 Pain Intensity, Follow-Up

For research question 1b, the follow-up measurement of pain (outcome variable `nrs_fu_1`) will be analysed as well, using the same method as described in Section 6.2.2. For the imputation of missing values, the following predictor variables will be used:

- pain intensity measured at follow-up (`nrs_fu_1`)
- effectiveness briefing group (EXPBRIEF)
- side effects briefing group (SIDEBRIEF)
- pain intensity at first visit (`screeningb_1a_4a`)
- pain intensity after acupuncture treatment (`nrs_8_1`)
- baseline optimism (`LOT_BL_optim`)
- baseline pessimism (`LOT_BL_pessim`)
- acupuncture therapist (`acupuncturist`)
- gender (`pers_1_2`)
- age (`age`)
- duration of pain at first visit (`painduration`)
- pain bothersomeness at baseline (`nrs_1a_2`)
- pain bothersomeness at the end of acupuncture treatment (`nrs_8_2`)
- depression (`PROMIS_BL_depression.theta`)
- CARE score (`CARE_1a_red1`)

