## **8.4 Data Collection and Follow-up for Withdrawn Participants**

We will assess possible reasons for withdrawal or dropout at the last visit before dropout. A follow-up of withdrawn patients is not intended.

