### **9.3.6 Visit 4**

Session 4 will be in the mid of the acupuncture treatment phase and hence, EAT (P2), PROMIS (P3) and NRS (P7) will be assessed after this session in addition to the normal session flow.

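### The SAP's predictor list for imputing week-4 pain (research question 1b) omits the same patient's week-2 pain: some precision is lost, and bias is possible if drop-out after session 4 depends on that score differently by arm

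*Combined protocol and SAP*

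**What the plan says.** SAP section 4.3 makes the imputation part of the primary analysis: "For research questions 1b, an intention-to-treat analysis will be performed using multiple imputation". Section 6.5 assumes missing at random, uses chained equations, and gives a closed list for 1b, introduced by "and the concomitant sensitivity analyses, the following variables will be used as predictors in the imputation process of missing values". The 13 entries are week-4 pain (nrs_8_1), the two briefing factors, first-visit pain, optimism, pessimism, therapist, gender, age, pain duration, baseline bothersomeness, depression and the CARE score. CARE is completed after the briefing but before the first needle (protocol 9.2.3). No entry other than the outcome is measured once acupuncture has started.

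A pain score from mid-treatment does exist:

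- SAP 6.1: "The NRS is filled in at baseline (before the treatment), after two weeks, and at the end of the acupuncture sessions".
- Protocol 9.3.6, on visit 4: "EAT (P2), PROMIS (P3) and NRS (P7) will be assessed after this session in addition to the normal session flow".
- SAP 6.6.2: "A second ANCOVA using the pain intensity obtained after the 4th acupuncture session (in week 2) as outcome will be performed".
- The glossary in SAP Appendix B lists it as nrs_4_1.

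For 6-month pain the plan does use earlier on-study scores. The list in SAP 6.6.5 includes "pain intensity after acupuncture treatment" (nrs_8_1) and end-of-treatment bothersomeness (nrs_8_2). On patients who withdraw, protocol 8.4 says: "A follow-up of withdrawn patients is not intended".

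**The concern.** Week-2 pain is probably the best available predictor of week-4 pain, and a plausible driver of who leaves in the second half of treatment. If drop-out after session 4 depends on it, missing at random need not hold given the listed predictors, but can hold once nrs_4_1 is added. A difference between arms is conceivable, because the two effectiveness briefings respond differently to a patient who is not improving (protocol 8.2.1 and 8.2.3).

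At stake is the estimate for a primary outcome whose planned power is only 56–65%. No sensitivity analysis covers the gap. Those for 1b are complete-case, exclusion of opioid users, at least 6 of 8 sessions, and extra covariates (SAP 6.4). None brings week-2 pain into the imputation.

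**Working it through.** **Inputs from the documents.** SMD 0.38 for 1b; two-sided alpha 0.05; 128 to 150 patients split equally; planned drop-out about 15% (SAP 3.3). SAP 4.2 says only that a few patients stopped acupuncture early, without count or timing.

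**Assumptions.** The documents give no NRS SD, no correlations between time points and no drop-out mechanism. Pain is put on an SD scale, with three sets of correlations.

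**The plan's own figures.** Power = Φ(d·√(n/2) − 1.96), with n per arm.

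- n = 64: 0.38 × √32 = 2.150; Φ(0.190) = 57.5% (t-test 56.9%).
- n = 75: 0.38 × √37.5 = 2.327; Φ(0.367) = 64.3% (t-test 63.8%).
- Enrolment: 128 / 0.85 = 150.6, against 150 stated.

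These agree with the plan to within rounding and method.

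**Large-sample bias.** One million simulated patients per scenario; all missing patients leave after session 4, at the same rate in each arm. The log-odds of leaving rise by 1 per SD of week-2 pain (odds ratio e¹ ≈ 2.7), either in one arm only or with opposite sign in the two arms. Week-4 pain is imputed by regression from arm and baseline pain, with or without week-2 pain, and then analysed by ANCOVA. Absolute bias in SD without week-2 pain:

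| Correlations: baseline/wk 2, baseline/wk 4, wk 2/wk 4 | One arm: 5% | 10% | 15% missing | Opposite: 5% | 10% | 15% missing |
|---|---|---|---|---|---|---|
| 0.4, 0.35, 0.6 | 0.024 | 0.044 | 0.063 | 0.041 | 0.083 | 0.127 |
| 0.5, 0.4, 0.7 | 0.020 | 0.046 | 0.065 | 0.047 | 0.094 | 0.141 |
| 0.4, 0.3, 0.8 | 0.033 | 0.061 | 0.090 | 0.062 | 0.126 | 0.184 |

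With week-2 pain added, no scenario exceeds 0.006. With equal dependence in both arms, or random drop-out, the bias is also at most 0.006 without it.

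**Hand check.** Bias in the affected arm ≈ p × β × Δ. Here p is the missing share, β the slope of week-4 on week-2 pain given baseline, and Δ the leaver-minus-stayer difference in baseline-adjusted week-2 pain. For the middle row, β = (0.7 − 0.5 × 0.4)/(1 − 0.5²) = 0.667. A bias of 0.065 at 15% implies Δ = 0.065/(0.15 × 0.667) = 0.65. At 5% the formula then gives 0.05 × 0.667 × 0.65 = 0.022, close to the simulated 0.020.

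**At trial size.** N = 150, 1,500 trials, 20 imputations, Rubin's rules, middle correlations. Drop-out is 15% in the random case. In the one-arm case it is 11.6% in the unlinked arm and about 15% in the linked (high-briefing) arm. Each cell gives listed predictors / with week-2 pain.

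| Drop-out | Estimate (true −0.38) | Type I error |
|---|---|---|
| Random | −0.379 / −0.378 | 5.7% / 5.2% |
| Same dependence in both arms | −0.365 / −0.378 | 5.2% / 4.7% |
| One arm only | −0.431 / −0.375 | 6.9% / 4.9% |
| Opposite | −0.501 / −0.374 | 12.6% / 3.9% |

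The simulation error of a 5% rate is √(0.05 × 0.95/1500) = 0.6 points. Under random drop-out with no true effect the SE falls from 0.164 to 0.158, and the share of variance due to missingness from 16% to 10%. With the planned effect, power rises from 63% to 65%. Direction follows the arm: here high-pain patients left the high-briefing arm, which exaggerates the benefit; the mirror case attenuates it.

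These runs used normal-model imputation. A run with predictive mean matching, the SAP's method (600 trials, 13–14% missing, one-arm dependence), gave −0.290 with the listed predictors, −0.363 with nrs_4_1 and −0.377 on full data. That shortfall of 0.377 − 0.290 = 0.087 SD lies at the top of the one-arm range.

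**The case against.** The case for leaving the plan alone has four parts, and much of it stands.

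- **Bias is conditional.** It needs drop-out after session 4 that depends on week-2 pain differently by arm. Nothing in the documents shows that this happened.
- **Timing limits the fix.** The remark to worsening patients in the regular arm belongs to the booster visit (protocol 8.2.3), held before session 2 (protocol 9.3.4). Anyone who leaves soon after it has no week-2 score. In a large-sample check with 10.5% missing and a log-odds slope of 2 in one arm, adding week-2 pain left the bias at 0.08 SD when all left before session 4, and at about 0.04 SD when half did. Drop-out driven by pain in weeks 3 and 4 is not repaired either.
- **Numbers are probably small.** The 15% is a planning figure, and the SAP, written after the last visit, speaks only of a few early stoppers.
- **The rest of the plan gives some protection.** Missing-data patterns and the fraction of missing information will be reported, and the imputation retains patients with missing baseline questionnaires.

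A reader might infer more than the documents support. One inference is that everyone who stopped acupuncture lacks week-4 pain; protocol 8.4 concerns withdrawn patients, and no passage says this of all stoppers. Another is that the imputation uses baseline data only; it also uses both briefing factors, therapist and the post-briefing CARE score. A third is that the effect will be attenuated by 19–30%. A simulation with SD 2 and a true effect of −0.80 points does give −0.65 to −0.56 at 10–11% missing, which is a bias of 0.15/2 = 0.075 to 0.24/2 = 0.12 SD. But a separate check needed an odds ratio above roughly 7 per SD of week-2 pain to reach about 0.095 SD at that missing rate.

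None of this gives a reason to leave the score out.

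**Conclusion.** The omission is real, and it does not follow from a general rule in the plan, since SAP 6.6.5 does the opposite for 6-month pain. Its sure cost is a little precision. Its possible cost, with dependence in one arm only, is about 0.02–0.03 SD at 5% missing and 0.06–0.09 SD at 15%. Against 0.38 SD that is roughly 5–8% and 16–24% of the planned effect. If the NRS SD is 1.5 to 2.5 points (assumed), the ranges are about 0.03–0.08 and 0.09–0.23 points. Opposite dependence in the two arms would double these figures but is a more extreme case.

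All sizes rest on assumed correlations, an assumed drop-out slope, and every leaver having reached session 4. It would be wrong to conclude that the planned analysis is biased, or that adding week-2 pain guarantees an unbiased one. The supported conclusion is that the addition makes missing at random more credible for a primary outcome and did no harm to bias or precision in these simulations.

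**What to change.** Amend the SAP, with a date, before any unblinded analysis; SAP 3.1 keeps the analysis blind to allocation, so this can be done cleanly.

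- Add nrs_4_1 to the 1b predictor list in section 6.5. The week-2 expectation score (EAT_4) and the number of sessions attended are optional further auxiliaries.
- Add nrs_4_1 to the follow-up list in section 6.6.5.
- Leave the ANCOVA unchanged. Week-2 pain is affected by the briefing, so it belongs in the imputation model and not among the adjustment variables.
- Report, by briefing arm, how many patients left before and after session 4 and how many lack week-4 pain. This shows how far the point matters.

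Two further ideas are not worth pursuing. End-of-treatment bothersomeness (nrs_8_2) is on the same form at the same visit as the outcome (protocol study schedule), so it will usually be missing with it. Mailing a week-4 pain form to patients who stopped is no longer possible, because the last patient visit was on 11 December 2017 (SAP 3.7).

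The cost is one to three extra variables in the imputation call and one short table.

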## 6.6 Analyses of Secondary Outcomes

### 6.6.1 Research question 1a

A second ANCOVA using the EAT score obtained after the 4th acupuncture session (in week 2) as outcome will be performed. The covariates and adjusting variables will be as described in Section 6.2.1.

### 6.6.2 Research question 1b

A second ANCOVA using the pain intensity obtained after the 4th acupuncture session (in week 2) as outcome will be performed. The covariates and adjusting variables will be as described in Section 6.2.2.

### 6.6.3 Research question 2

A secondary outcome for research question 2 is the total side effect score for each patient, which will be adjusted for the number of acupuncture sessions that the patient actually received minus 1. For a patient with the number of sessions given by  $N_s$ , the outcome is thus

$$\text{Total score} = \frac{(\text{Score}_1 + \text{Score}_2 \dots + \text{Score}_{N_s-1})}{N_s - 1} \cdot 7.$$

As this may lead to total score values that are non-integers, the total score will be rounded to the next integer. A zero-inflated negative binomial model with SIDEBRIEF and gender (`pers_1_2`) will be

used. As for the primary analysis (Section 6.2.3), the result from the zero-inflated negative binomial regression will be reported as the ratio of side effect scores with 95% confidence interval and  $p$ -value. In addition, adjusted means of the total side-effects scores with 95% confidence intervals will be reported for each treatment group, where the gender effect will be weighted with 0.5.

#### 6.6.4 2 x 2 Factorial Analyses

Two additional analyses of research questions 1a and 1b will be performed using the two main factors effectiveness briefing (EXPBRIEF) and side effects briefing (SIDEBRIEF) together in the same model. Missing values will be imputed.

#### 6.6.5 Pain Intensity, Follow-Up

For research question 1b, the follow-up measurement of pain (outcome variable `nrs_fu_1`) will be analysed as well, using the same method as described in Section 6.2.2. For the imputation of missing values, the following predictor variables will be used:

- pain intensity measured at follow-up (`nrs_fu_1`)
- effectiveness briefing group (EXPBRIEF)
- side effects briefing group (SIDEBRIEF)
- pain intensity at first visit (`screeningb_1a_4a`)
- pain intensity after acupuncture treatment (`nrs_8_1`)
- baseline optimism (`LOT_BL_optim`)
- baseline pessimism (`LOT_BL_pessim`)
- acupuncture therapist (`acupuncturist`)
- gender (`pers_1_2`)
- age (`age`)
- duration of pain at first visit (`painduration`)
- pain bothersomeness at baseline (`nrs_1a_2`)
- pain bothersomeness at the end of acupuncture treatment (`nrs_8_2`)
- depression (`PROMIS_BL_depression.theta`)
- CARE score (`CARE_1a_red1`)

### 6.6.6 Perceived Sensitivity to Medicines Score, PSM

The PSM score will be analyzed using three ANCOVA models (no imputation):

```
PSM_8 ~ SIDEBRIEF + pers_1_2 + PSM_BL
```

```
PSM_8 ~ SIDEBRIEF + pers_1_2 + LOT_BL_optim + LOT_BL_pessim +  
acupuncturist + PSM_BL
```

```
PSM_8 ~ SIDEBRIEF + pers_1_2 + LOT_BL_optim + LOT_BL_pessim +  
acupuncturist + age + painduration + CARE_1a_red1 + PSM_BL
```

### 6.6.7 Post-treatment Guess

After the study, patients and acupuncturists were asked to guess in which effectiveness briefing and in which side effect briefing group they had been randomized.

The agreement between the patients and the acupuncturists will be assessed using four chi-square ( $\chi^2$ ) tests:

- postguessp\_8\_1 vs. EXPBRIEF
- postguessa\_8\_1 vs. EXPBRIEF
- postguessp\_8\_3 vs. SIDEBRIEF
- postguessa\_8\_3 vs. SIDEBRIEF

## 6.7 Further Analyses

A list of further inquiries into the data set, defined by [name] and [name], is provided in Appendix A. The models to be fitted are described in R syntax. A glossary of the variable names is provided in Appendix B.

## 6.8 Harms

The side effects of the acupuncture treatment are central to research question 2 and will be analyzed as discussed in Section 6.2.

## 6.9 Statistical Software

The analyses described in this SAP will be performed in the R programming language (R Core Team, 2017) (version 3.4.4) running on Linux Ubuntu 16.04 LTS.

Required R packages are mentioned in the respective sections of this document.

## 7 Separate Analyses

Additional analyses will be conducted within the PhD project by [name] and [name]. Separate SAPs will be written.

## A Additional Analyses of Secondary Outcomes

### A.1 Baseline With Covariates

PROMIS\_8\_anxiety.theta ~ EXPBRIEF + pers\_1\_2 + LOT\_BL\_optim +  
LOT\_BL\_pessim + acupuncturist + PROMIS\_BL\_anxiety.theta

PROMIS\_8\_depression.theta ~ EXPBRIEF + pers\_1\_2 + LOT\_BL\_optim +  
LOT\_BL\_pessim + acupuncturist + PROMIS\_BL\_depression.theta

PROMIS\_8\_fatigue.theta ~ EXPBRIEF + pers\_1\_2 + LOT\_BL\_optim +  
LOT\_BL\_pessim + acupuncturist + PROMIS\_BL\_fatigue.theta

PROMIS\_8\_paininterference.theta ~ EXPBRIEF + pers\_1\_2 + LOT\_BL\_optim +  
LOT\_BL\_pessim + acupuncturist + PROMIS\_BL\_paininterference.theta

PROMIS\_8\_physfunct.theta ~ EXPBRIEF + pers\_1\_2 + LOT\_BL\_optim +  
LOT\_BL\_pessim + acupuncturist + PROMIS\_BL\_physfunct.theta

PROMIS\_8\_sleep.theta ~ EXPBRIEF + pers\_1\_2 + LOT\_BL\_optim +  
LOT\_BL\_pessim + acupuncturist + PROMIS\_BL\_sleep.theta

PROMIS\_8\_participation.theta ~ EXPBRIEF + pers\_1\_2 + LOT\_BL\_optim +  
LOT\_BL\_pessim + acupuncturist + PROMIS\_BL\_participation.theta

promis\_8\_29 ~ EXPBRIEF + pers\_1\_2 + LOT\_BL\_optim + LOT\_BL\_pessim +  
acupuncturist + promis\_1a\_29

nrs\_8\_2 ~ EXPBRIEF + pers\_1\_2 + LOT\_BL\_optim + LOT\_BL\_pessim +  
acupuncturist + nrs\_1a\_2

